**Methods/design:**

This randomized, sham-controlled, participant-blinded and assessor-blinded pilot trial is underway in China. A total of 60 participants with CU will be randomly assigned to two groups in a 1:1 ratio: one treated with real acupuncture and the other with sham acupuncture, for 10 sessions over 2 weeks. The experimental group will receive acupuncture on a fixed prescription of acupoints, whereas the control group will receive sham acupuncture, namely minimal acupuncture on non-acupuncture points. The primary outcome will be the urticaria activity score (UAS). The secondary outcomes will include a visual analogue scale (VAS) score for itching intensity, the Dermatology Life Quality Index (DLQI), the Hamilton Depression Scale (HAMD), the Hamilton Anxiety Scale (HAMA), the humoral immunity index, serum total IgE, and adverse events. The UAS, VAS for itching and the DLQI will be conducted at baseline and at 1, 2, 3, and 4 weeks after randomization. The HAMD, HAMA, humoral immunity index, and serum total IgE will be assessed at baseline and at 2 weeks after randomization. Adverse events will be summarized at 1 week and 2 weeks after randomization.

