### Setting of the study

This clinical trial will be conducted at the Affiliated Hospital of Chengdu University of Traditional Chinese Medicine. Eligible participants will be randomly assigned to the experimental group (*n* = 30) or the control group (*n* = 30) with a 1:1 ratio. The total observation period will be 5 weeks, including a 1-week baseline period, a 2-week treatment period and a 2-week follow-up period. They will receive 10 sessions of acupuncture or sham acupuncture treatment over 2 weeks (five sessions per week). During the baseline, treatment, and follow-up periods, participants will not be allowed to take any therapeutic medications (e.g., antihistamine, omalizumab, and CsA) for CU. but will be permitted to use antihistamines as necessary (e.g., loratadine, ebastine, and mizolastine) when the wheals and itching are unbearable. The number of wheals, degree of itching, impact on life, and medical history will be recorded in urticaria diaries every day. Assessments will be conducted at baseline and at 1, 2, 3, and 4 weeks after randomization. Figure 1 illustrates the study flowchart. The reporting of this trial is conducted according to the Standard Protocol Items: Recommendations for Intervention Trials (SPIRIT) guidelines [28] (Additional file 1), and the Standards for Reporting Interventions in Clinical Trials of Acupuncture (STRICTA) [29] have been used as frameworks of methodology for designing this protocol (Additional file 2).

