#### Primary outcome

The primary outcome measurement is the urticaria activity score (UAS) [1, 31]. The UAS, which is used to make daily assessments for 1 week, combines daily wheal numbers (0 = none, 1 = < 20 wheals/24 h, 2 = 20–50 wheals/24 h, and 3= > 50 wheals/24 h or large confluent areas of wheals) and pruritus intensity (0 = none, 1 = present but not annoying or troublesome, 2 = troublesome but does not interfere with normal daily activity or sleep, and 3 = severe pruritus, which is sufficiently troublesome to interfere with normal daily activity or sleep). It has a total score of 42 points for 1 week. The primary outcome measurement will be assessed at baseline and at 1, 2, 3, and 4 weeks after randomization.

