##### Adverse events

The participants will be requested to voluntarily report information about adverse events such as pallor, sweating or dizziness, fainting during acupuncture treatment, bleeding, local hematoma, unbearable prickling, and continuous severe pain more than 1 h after acupuncture. The acupuncturists will be requested to report adverse events related to the acupuncture such as sticking of the needle, broken needles, bent needles, and needles being retained after treatment. All adverse events will be fully recorded on the adverse event pages of the case report forms (CRFs). The researcher will confirm the occurrence of adverse events and record all details such as the date of occurrence, time, degree, measurement related to the treatment, and causal relationship with the treatment. Emergency medical assistance will be sought if any serious adverse effect occurs, and all details will be noted. The outcome measurement will be assessed at 1 and 2 weeks after randomization.

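### Scheduled adverse-event assessment ends at week 2 although outcome assessments run to week 4, so the safety summary could be incomplete for the 2-week follow-up

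*Protocol article*

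**What the plan says.** The Adverse events section gives the schedule as "The outcome measurement will be assessed at 1 and 2 weeks after randomization". The abstract (Methods/design) agrees: "Adverse events will be summarized at 1 week and 2 weeks after randomization".

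The Setting of the study section describes a longer period of observation: "The total observation period will be 5 weeks, including a 1-week baseline period, a 2-week treatment period and a 2-week follow-up period". It then says "Assessments will be conducted at baseline and at 1, 2, 3, and 4 weeks after randomization". The Primary outcome section repeats those times for the UAS, and the VAS and DLQI sections do the same.

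On how events are found, the Adverse events section names two sources. One is the participants: "The participants will be requested to voluntarily report information about adverse events". The other is the treating staff: "The acupuncturists will be requested to report adverse events related to the acupuncture". A researcher then confirms each event, with its date and its relation to treatment. The section also promises complete recording of all events on the case report form and gives no end date for this.

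Safety is among the pilot's aims in the Abstract, the Background and the Sample size estimation section. The Statistical analysis section plans a between-group comparison of adverse events.

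**The concern.** Two outcome assessments, at weeks 3 and 4, take place with no adverse-event assessment attached to them, in a pilot that is meant to inform a full trial on safety. The article states the schedule twice and consistently, so this is a design choice and not a detail left to a fuller document.

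Two kinds of event could be affected. The first is a delayed local reaction to the last few sessions, which have little scheduled observation time behind them. The second is angioedema in follow-up. It belongs to the disease definition used for inclusion, and the Discussion anticipates that it may become unbearable during the study. The UAS as described scores only wheals and itch, and the listed diary items do not name angioedema or adverse events.

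At stake is whether the reported adverse-event frequency, and the comparison between arms, can be read as applying to the whole study period.

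**Working it through.** **Inputs**
- Observation period: 1 week baseline, 2 weeks treatment, 2 weeks follow-up (Setting of the study).
- Sessions: once daily for 5 days, then 2 days' rest, 10 sessions over 2 weeks (Interventions).
- Adverse-event assessments: weeks 1 and 2 (Abstract; Adverse events).
- UAS, VAS and DLQI after baseline: weeks 1, 2, 3 and 4 (Abstract; the three outcome sections).
- Assumptions: the first session is on day 1 after randomisation, and the week 2 assessment is on day 14.

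**Step 1: the plan's own figures.** 1 + 2 + 2 = 5 weeks, and 5 × 2 = 10 sessions. Both agree with the article. The time after randomisation is 2 + 2 = 4 weeks, or 28 days.

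**Step 2: coverage.** Scheduled adverse-event assessment covers days 1 to 14. The uncovered part is 28 − 14 = 14 days, and 14/28 = 50%. By assessment, 2 of the 4 post-baseline assessments include adverse events.

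**Step 3: time from the last session to the last check.** Sessions fall on days 1 to 5 and 8 to 12. The gap is 14 − 12 = 2 days. If the first session comes k days later, the gap is 2 − k days: 1 day for k = 1 and none for k = 2. A later start therefore only shortens it.

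**Step 4: what else could pick up an event in days 15 to 28**

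| Source | What the article describes | Would it find a late event? |
|---|---|---|
| Participant report | Voluntary; no standard questioning described | Only if volunteered |
| Acupuncturists | Needling-related events | No treatment sessions after week 2 |
| Diary | Wheals, itching, impact on life, medical history | Wheals and itch yes; no named item for angioedema or other events |
| UAS | Wheal count and itch | Angioedema not scored |
| Case report form | All events recorded, no end date | Only once someone has reported the event |

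**Step 5: effect of the fix.** With assessments added at weeks 3 and 4, coverage is 28 of 28 days and 4 of 4 assessments. Time from last session to last check becomes 28 − 12 = 16 days under the day-1 assumption. The sample size of 60 does not change.

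**The case against.** The strongest defence is that the window matches the exposure. All 10 sessions fall in weeks 1 and 2, and the events the article lists (fainting, bleeding, haematoma, prickling, prolonged pain, needle problems) arise during or soon after needling. Half the calendar is not half the risk. This stands, and it limits how many events a longer window would add. It does not cover angioedema or slower local reactions.

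Several stronger readings are tempting, and the document does not support them.

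- **That follow-up events are missed, or that follow-up has no adverse-event data.** Recording on the case report form has no cut-off date, so a late event that is volunteered can still be entered. What is absent is a scheduled assessment.
- **That all ascertainment rests on voluntary reports.** That describes the participant route only. Acupuncturists are asked separately, and a researcher confirms events. Participants are also asked to report, with example events named. The article gives no figure from which undercounting could be measured.
- **That the reported rate would be too low.** It could be incomplete; nothing in the document shows by how much.
- **That disease flares go unobserved.** Wheals and itch are followed to week 4 by diary and UAS.
- **That the small sample makes the short window worse.** With no events in 30 participants, the one-sided 95% upper bound is 1 − 0.05^(1/30) = 0.095. That depends on the number of participants and would be the same with assessment to week 4. It is no evidence about the window, and the Discussion already concedes that the sample is small.

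The timetable figure (Fig. 2) is not available in the text reviewed and could not be checked. The two text statements agree with each other, so the point rests on them.

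**Conclusion.** The point holds in limited form. The article fixes adverse-event assessment at weeks 1 and 2 only, leaving 14 of 28 post-randomisation days (50%) and 2 of 4 post-baseline assessments without it. On the day-1 assumption the last check falls about 2 days after the last session. Late events, including delayed local reactions and angioedema, depend on being volunteered and may fall outside the planned summary, so the reported frequency could be incomplete for follow-up.

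How many events are at issue cannot be estimated from the document and is probably small. The primary outcome, the sample size and the efficacy analysis are unaffected. The change is still worth making, because safety is a declared aim and the assessments needed already exist.

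**What to change.** At the existing week 3 and 4 assessments, have the blinded assessor put one standard open adverse-event question to every participant, worded identically in both arms. Follow it with the participant-reported items listed in the Adverse events section. The needle-handling items (stuck, bent, broken or retained needles) should stay with the acupuncturists, to whom the article assigns them. Summarise adverse events over weeks 1 to 4, split into treatment and follow-up, and amend the abstract and the Adverse events section to match.

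If collection is not extended, state that adverse-event data are limited to the treatment period, give the reason, and confine the safety conclusion to that period.

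The cost is a few minutes at two assessments that already take place, and possibly slightly higher adverse-event counts. The number of participants does not change.

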### Sample size estimation

This study aims to evaluate clinical trial feasibility and to investigate basic information about the effects and safety of acupuncture for the treatment of CU, rather than hypothesis testing. Therefore, the sample size was decided based on a rationale for feasibility, precision around the mean and variance, and regulatory considerations and ethical issues that prohibit over-recruitment of participants [41]. Considering an estimated 20% dropout rate, we ensured that the sample size exceeded the minimal number needed to assure the validity of the mean, effect size, and rationale of feasibility. Accordingly, a required sample size of 60 participants was estimated.

### Data collecting and monitoring

The Evidence-based Medicine Center of Chengdu University of Traditional Chinese Data is the Monitoring Committee for Medical Data in this study. Data will be recorded by designated outcome assessors on the paper CRFs, and double-entered into the electronic CRFs, which are established and monitored by the Evidence-based Medicine Center of Chengdu University of Traditional Chinese Medicine. Monitors will audit the data every 3 months. Acupuncturists and statisticians will have no access to these data during the evaluation process.

### Statistical analysis

All data will be presented as means and standard deviations or number (percentage), and all analyses will be based on the intention-to-treat principle. For the description of baseline characteristics, the mean with standard deviation or range with the minimum and maximum values for continuous data and frequency with percentage for dichotomous data will be reported. Homogeneity between the two groups in terms of baseline characteristics will be tested using the two-sample *t* test for continuous data and the chi square (χ2) test for dichotomous data. Analysis of covariance (ANCOVA) or logistic regression will be used for analysis and adjustment of baseline characteristic that differ significantly between the two groups.

The primary outcome of this study is the cumulative UAS in each group. After a normality test, the total score will be compared using the independent *t* test (parametric) or the Mann-Whitney U test (non-parametric) according to the normality of the data. In secondary outcome analysis, the VAS score for itching intensity and the DLQI will be used to analyze the difference, and differences between groups in mean change between baseline and measurements made at 1, 2, 3, and 4 weeks will be analyzed by repeated measures two-factor analysis. The HAMA, HAMD, humoral immunity index, and serum total IgE measurement will be compared using the independent *t* test (parametric) or the Mann-Whitney U test (non-parametric) according to the normality of the data. The χ2 test or logistic regression will be used to analyze dichotomous outcomes. Adverse events will be compared between groups using the χ2 test or Fisher’s exact test. Missing values will be replaced using the method of last observation carried forward. If the participant dropout rate is > 20%, sensitivity analysis will be conducted with the data included.

All statistical tests will be two-sided, and *p* < 0.05 will be considered statistically significant. The statistical software of SPSS (SPSS, SPSS Inc., Chicago, USA) version 21.0 will be used for the analysis.

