The chosen primary outcome is change in the symptom of wheals and angioedema as obtained from the 7-day UAS. Multiple guidelines [1, 15] and a consensus statement [3, 16] recommend the UAS as the main outcome, and the UAS had been widely used as an outcome measure in CU studies. At the same time, assessment of the severity of CU has mainly depended on patient-reported outcomes. The VAS score for itching intensity can directly assess the variations in the severity of subjective symptoms. The available data indicate that urticaria markedly affects both objective functioning and subjective well-being [56–58]. In this trial, we use the DLQI to evaluate quality of life in patients with CU before and after acupuncture treatment. The DLQI is extensively used in evaluating quality of life in skin disease. It is safe and convenient, and also various different language versions of the DLQI are more readily available than the CU Quality of Life Questionnaire (CU-Q2oL) and the Angioedema Quality of Life Questionnaire (AE-QoL). We have obtained the authorization of the Chinese version of DLQI from Finlay [36]. We will also test for correlation between the symptoms of CU and psychiatric disorders by evaluating the HAMD and HAMA in this study. The Humoral immunity index and measurement of serum total IgE will be experimentally assessed to evaluate possible correlation between immunity and the mechanism of the effects of acupuncture on CU.

This trial has its limitations. First of all, this clinical trial will include a small population of participants and will not primarily aim to perform hypothesis testing. For this reason, the results of this study cannot be generalized as basic data for assessing the effect and safety of acupuncture for treatment of CU. Furthermore, because the control group will receive minimal acupuncture, we cannot ignore the possibility of physiological activation caused by needle penetration. The effect of acupuncture will need to be carefully interpreted because the acupuncture points, needling depth, and *de-qi* will be the only differences assessed between groups.

To summarize, this study is funded by the National Key Research and Development Program of the China-Key Project. The study protocol describes the first randomized, patient-blinded and assessor-blinded, sham-controlled trial. The findings of the study will provide feasibility data and basic information about the effect and safety of acupuncture for a future, full-scale RCT in CU.

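### The primary UAS outcome is a total score in the analysis section but a change in the Discussion, and no deciding week is named

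*Protocol article*

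**What the plan says.** The Primary outcome section builds the UAS from daily wheal and pruritus scores over one week and gives the scale: "It has a total score of 42 points for 1 week". On timing it says: "The primary outcome measurement will be assessed at baseline and at 1, 2, 3, and 4 weeks after randomization".

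The Statistical analysis section says: "The primary outcome of this study is the cumulative UAS in each group". A check of normality then selects the method for this comparison, in these words: "the total score will be compared using the independent *t* test (parametric) or the Mann-Whitney U test (non-parametric) according to the normality of the data". No week, accumulation window or baseline term is given for it. ANCOVA appears in that section only for baseline characteristics that turn out to differ significantly between groups.

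The Discussion says: "The chosen primary outcome is change in the symptom of wheals and angioedema as obtained from the 7-day UAS". It gives no time point for the change.

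For the VAS and DLQI, which follow the same visit schedule, the Statistical analysis section is more specific and plans a longitudinal analysis of change: "differences between groups in mean change between baseline and measurements made at 1, 2, 3, and 4 weeks will be analyzed by repeated measures two-factor". The UAS is not included there. The same section sets the criterion: "All statistical tests will be two-sided, and *p* < 0.05 will be considered statistically significant".

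**The concern.** A primary outcome needs one metric, one time point (or one defined window) and one comparison. Here the analysis section tests a level and the Discussion names a change, and the change has no matching primary analysis. Treatment lasts two weeks and is followed by two weeks without it. A week-2 result therefore describes the effect at the end of treatment, and a week-4 result describes whether it persists. These are different questions, and the text does not choose between them.

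Two things are at stake. First, the reported primary result could be chosen after the data are seen, while a p < 0.05 criterion applies to all tests. Second, the Discussion lists initial primary-outcome data for sizing a larger trial among the purposes of pilot studies. An effect picked from several candidates tends to be too large, and the standard deviation carried forward depends on whether score or change is used.

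**Working it through.** **Scale.** The daily maximum is 3 (wheals) + 3 (pruritus) = 6, and 7 × 6 = 42. The article's 42 points per week is reproduced, so its total score is a 7-day sum.

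**Candidates.** Two metrics (score, change from baseline) × four weeks = 8. If *cumulative* meant a sum over weeks, the ranges would be 0–84 (2 × 42) or 0–168 (4 × 42). No section mentions such a sum.

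**Size of the selection risk (illustration).** Inputs from the article are 30 per group, four post-baseline weeks and two-sided 0.05. With the 20% dropout allowance, 30 × 0.8 = 24 per group. The correlation between UAS measurements is not given, so I assumed 0.3 to 0.9, either equal between all visits or decaying with time (AR(1)).

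For four independent tests the chance of at least one p < 0.05 under no effect is 1 − 0.95⁴ = 0.185. Simulated values for correlated normal data (10,000 runs, two-sample t tests, 30 per group) are:

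| Correlation | Score, 4 weeks: equal | Score, 4 weeks: AR(1) | Score and change, 4 weeks: equal | Score and change, 4 weeks: AR(1) |
|---|---|---|---|---|
| 0.3 | 0.175 | 0.183 | 0.279 | 0.275 |
| 0.5 | 0.155 | 0.167 | 0.265 | 0.254 |
| 0.7 | 0.130 | 0.142 | 0.255 | 0.244 |
| 0.9 | 0.096 | 0.109 | 0.234 | 0.217 |

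With 24 per group the four-week range is 0.092–0.181, which is practically the same. Overall that is about 9–18% for the four scores and 22–28% for all eight variants. A single pre-named quantity (simulated as the four-week sum) gave 0.046–0.052, as it should.

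**Effect on planning figures.** Let ρ be the correlation between baseline and the chosen week, with equal variances and the raw score's variance set to 1. Change has variance 2(1 − ρ), and a baseline-adjusted comparison has residual variance 1 − ρ².

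| ρ | Score | Change | Baseline-adjusted |
|---|---|---|---|
| 0.3 | 1.00 | 1.40 | 0.91 |
| 0.5 | 1.00 | 1.00 | 0.75 |
| 0.7 | 1.00 | 0.60 | 0.51 |
| 0.9 | 1.00 | 0.20 | 0.19 |

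For a given difference and power, the next trial's size is proportional to this variance, so the unresolved choice of metric feeds directly into it.

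**Why baseline adjustment settles score against change.** Write the week's score as Y = a + bT + cB, with T the treatment group and B the baseline score. Subtracting B gives Y − B = a + bT + (c − 1)B. The treatment difference b is the same in both.

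**The case against.** A reader might infer that the article gives three incompatible definitions: weekly, cumulative and change. The text does not support that. The Primary outcome section uses *total score* for the 7-day sum, and *cumulative* most naturally means the same thing. Two metrics compete, not three.

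The change version rests on one Discussion sentence that is loosely worded. It speaks of angioedema, which the UAS as defined in the article does not score. It may be an editorial slip rather than a rival endpoint, but it still states the primary outcome differently from the analysis section and needs reconciling.

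A reader might also take the 9–18% as the error rate of the plan. It is not. The correlations are assumed, and the Statistical analysis section describes one comparison, not four tests with any positive result reported.

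The pilot status counts for a good deal. The Sample size estimation section says the aim is feasibility and basic information rather than hypothesis testing, and the Discussion repeats that this is not the primary aim. This lowers the severity. It does not remove the point, because the p < 0.05 criterion covers all tests and the Discussion mentions sizing a larger trial.

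Finally, this is a condensed article, and a fuller document may name the week. That could account for the missing time point. It does not account for the disagreement between score and change, which is visible in the article itself.

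**Conclusion.** The point holds in this form: score and change are not reconciled, and no week or window is named as decisive, so the primary result is not determined by the text. Eight variants fit the wording on the natural reading of *cumulative*. The false-positive figures show the scale of the risk under assumed correlations of 0.3–0.9 and normal data, and only if every week were tested and the best reported.

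For a declared pilot this should be corrected but does not undermine the trial. It would also go too far to say that the documents dictate week 2: it is a reasonable choice, and week 4 would answer a different but legitimate question. The longitudinal analysis of the VAS and DLQI shows that more specific wording was available; using another method for the UAS is not itself an error.

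**What to change.** Before unblinding, align the Primary outcome section, the Statistical analysis section and the Discussion on one statement:

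- Primary quantity: the 7-day UAS (0–42) at one named week, for example week 2, the end of treatment.
- Primary analysis: the between-group mean difference with its confidence interval, from an ANCOVA with baseline 7-day UAS as a pre-specified covariate, whether or not the groups differ at baseline. This replaces the single unadjusted two-sample test for the primary outcome.
- Wording: state that cumulative UAS and total score mean the 7-day sum, and bring the Discussion sentence into line with the UAS as defined (wheals and pruritus).
- Other weeks: report them as secondary.

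The cost is a dated wording change in the protocol and, where they exist, in the analysis plan and registry entry. Baseline and all four weekly scores are already scheduled, so no new data are needed. The article describes the trial as ongoing, so the date of the change relative to unblinding should be recorded.
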